- 1. **Justification**

Actinic keratoses account for 10% of dermatological consultations in Brazil (Miot et al., 2018). However, the annual risk of progression of this type of lesion to squamous cell carcinoma (SCC) is 0.025%–0.6%, patients with multiple lesions face a risk of up to 20% for the emergence of carcinoma (Guorgis et al., 2020). Furthermore, these lesions are reported to have a significant impact on individuals' quality of life as they cause pain and bleeding in photo-exposed areas, leading to limitations and promoting stigmas related to appearance. This can interfere with social interactions, professional activities, leisure, and self-esteem (Vilhena et al., 2022). Consequently, there is substantial interest in exploring alternative therapeutic options, with the topical application of methyl aminolevulinate (MAL) followed by photodynamic therapy (PDT) irradiation considered one of the most promising approaches. This method is less destructive and selective and can also be used to treat cancerization fields. The higher selectivity of porphyrin precursors for diseased cells is crucial for the superior aesthetic results of this method compared to others. However, it can also cause discomfort, such as pain and burning, for a few minutes during photoactivation and several hours afterward due to the inflammatory reaction, lasting about two hours for MAL and six hours for 5-aminolevulinic acid (5-ALA), highlighting the need for protocols to mitigate adverse events.

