**2.2. Specific Objectives**

**•** To evaluate complete remission (100% remission) of the lesions in relation to the initial number of facial lesions at 3 months (primary objective);

• To evaluate complete remission (100% remission) of the lesions in relation to the initial number of facial lesions at other time points: 30 days, 9 months, and 12 months;

• To evaluate treatment success (75% reduction in the initial number of lesions in the treatment area compared to baseline) at 30 days, 3, 6, and 12 months;

• To evaluate the recurrence rate (reappearance of lesions in previously treated areas) at 30 days, 3, 6, and 12 months;

• To prevent squamous cell carcinoma (conduct assessments to verify the occurrence of squamous cell carcinoma. Cases will be recorded and treated as necessary. Evaluations will be carried out at 30 days, 3, 6, and 12 months);

• To evaluate the incidence of adverse effects through participants’ self-completed diaries and researcher notes. Assessments will be conducted at 30 days, 3, 6, and 12 months;

• To assess postoperative pain, if it occurs, after treatments using the visual analog scale (VAS) at 0 days, 30 days, 3, 6, and 12 months;

• To evaluate the amount of analgesics consumed weekly during the first week after treatment;

• To assess improvements in skin texture, wrinkles, and pigmentation using the scale by Tina Alster et al. (2005) at 30 days, 3, 6, and 12 months;

• To assess participants' quality of life using the Actinic Keratosis Quality of Life questionnaire (AKQoL) (Vilhena et al., 2022) after 6 months of treatment;

• To assess participants' quality of life using the Face-Q questionnaire (Klassen et al., 2015) after 6 months of treatment.

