• **Incidence of adverse effects -** The incidence of adverse effects, such as erythema, edema, itching, and peeling, will be monitored through a personal diary kept by the participant, in which detailed descriptions of any adverse effects will be recorded. As Jansen et al. (2019) recommended, this method will allow participants to report their symptoms individually. The principal investigator, a dermatologist specializing in this type of treatment, will offer continuous assistance and follow-up, remaining accessible as needed.

• **Subjective pain assessment** - Subjective pain will be assessed using the Visual Analog Scale (VAS), consisting of a 10-mm line with closed ends, indicating "0" for no pain and "10" for unbearable pain, the worst pain ever felt. The same operator will consistently provide instructions for marking the scale. Each participant will be instructed to mark with a vertical line the point that best reflects the intensity of their pain at the time of assessment, following the guidelines of Bottega et al. (2010). These assessments will be conducted weekly for up to 30 days after treatment, followed by evaluations at 3, 6, and 12 months.

[figure not shown]

Figure X: VAS - Visual Analog Scale for Pain. Source: the author

**Rescue Medication**: Rescue medication will be assessed by the standardized amount of analgesics consumed (paracetamol). At the start of the study, each participant will receive a blister pack of paracetamol®, a drug with purely analgesic effects, as Jóźwiak-Bebenista (2014) recommended. Participants are instructed to keep the blister pack until the end of the experiment and bring it to each appointment. At the end of the study, the number of tablets used will be evaluated in each group as a pain measurement parameter. In cases of reported allergy during anamnesis, dipyrone or ibuprofen may be prescribed as alternatives (WAHBA, 2004; TOMS, 2010).

• **Evaluation of Skin Texture, Wrinkles, and Pigmentation**: This evaluation will be conducted at 30 days, 3, 6, and 12 months, using the scale by Tina Alster et al. (2005). This scale, assessed by professionals and participants, classifies improvements as minimal (<25%), moderate (25%-50%), significant (51%-75%), and excellent (>75%). These evaluations will provide a comprehensive approach to measuring the effectiveness of the treatment over time.

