Participant Satisfaction – This will be assessed using the Actinic Keratosis Quality of Life questionnaire (AKQoL) (Esman et al., 2013) after 6 months and 1 year of treatment. The items will be scored on a standard 4-point Likert scale and summarized into a maximum score of 32 points. A higher score indicates greater impairment in quality of life. The questionnaire has been translated and validated into Portuguese (Vilhena et al., 2022).

EVALUATION OF SATISFACTION WITH FACIAL APPEARANCE (FACE-Q)

The FACE-Q scale (Satisfaction with Facial Appearance Overall) was developed by Klassen (Klassen et al., 2010) and consists of 10 items to be answered using a four-point Likert scale, which measures satisfaction with facial appearance in various scenarios. A Likert scale consists of a set of items in which the subject being evaluated is asked to indicate their level of agreement, ranging from "strongly disagree" (level 1) to "strongly agree" (level 4). The FACE-Q evaluates the perception of facial appearance in terms of characteristics such as symmetry, harmony, proportion, freshness or vitality, temporal appearance (e.g., rested facial appearance, at the end of the day, or upon waking), appearance under brighter lighting, appearance in photographs, and profile (lateral view or contour of the face). Despite being recent, the scale has already been used in several studies (Chang et al., 2016; Sinno et al., 2015; Kappos et al., 2017). Its adaptation to Brazilian Portuguese was carried out by Gama in 2018. The FACE-Q scale, validated for use in Brazil (Table 6), consists of nine items that measure two satisfaction factors (Overall facial appearance and Facial geometry). The item "With the appearance of your face at the end of the day" from the original scale was removed in the Brazilian version due to its low representativeness in the Brazilian sample, and for calculation purposes, it was also excluded from the evaluation in the present study. The sum of the scores obtained from patients' responses to the 9 items (1 = very dissatisfied, 2 = somewhat dissatisfied, 3 = somewhat satisfied, and 4 = very satisfied) can range from 9 to 36 and are converted into a score ranging from zero to 100. Higher scores indicate greater satisfaction (Table 7). The participants answered the FACE-Q questionnaire adapted to Brazilian Portuguese (Appendix C) before treatment and 30 days after its completion.

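### Sections 2.2 and 3.10 conflict on when pain and analgesic use are measured, and section 3.10 as written fixes no pain reading on the treatment day

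*Protocol*

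**What the plan says.** **Pain timing.** Section 2.2 (Specific Objectives) asks for postoperative pain "using the visual analog scale (VAS) at 0 days, 30 days, 3, 6, and 12 months". Section 3.10 (Study Outcomes) gives another schedule: "These assessments will be conducted weekly for up to 30 days after treatment, followed by evaluations at 3, 6, and 12 months". Section 3.10 also says that each mark should reflect "the intensity of their pain at the time of assessment". The scale is described as "consisting of a 10-mm line with closed ends", with its ends labelled 0 and 10.

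**When the pain occurs.** The Justification places pain and burning in the minutes of photoactivation and in the inflammatory reaction that follows, "lasting about two hours for MAL and six hours for 5-aminolevulinic acid (5-ALA"). It then argues for protocols that mitigate such events, and expects lower concentrations to reduce adverse effects.

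**Analgesics.** Section 2.2 sets the objective: "To evaluate the amount of analgesics consumed weekly during the first week after treatment". Section 3.10 defines the measure as paracetamol and states: "At the end of the study, the number of tablets used will be evaluated in each group as a pain measurement parameter". The Medication Treatment text before section 3.10 prescribes paracetamol for 3 days if pain occurs. It allows dipyrone for paracetamol allergy, ibuprofen as a further alternative, and ketorolac for severe pain not relieved by the earlier medication.

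**FACE-Q.** Section 2.2 and the Abstract place follow-up at 6 months. The FACE-Q text in section 3.10 says "before treatment and 30 days after its completion".

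**The concern.** Sections 2.2 and 3.10 cannot both be followed. The one that defines the outcomes leaves out the only treatment-day reading. Because the VAS asks about pain at the moment of marking, a later reading cannot recover what was felt during or shortly after illumination.

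Pain is a secondary outcome, but it bears on why the trial is run. The introduction names pain as an adverse event that has limited use of the procedure, and the Justification hopes a lower concentration will be better tolerated. If treatment-day pain is not recorded, no later analysis plan can supply it.

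The analgesic outcome has a similar weakness. A total evaluated at the end of a 12-month study does not answer a first-week question unless the first week can be separated out. A count of one drug also does not measure total analgesic use when four are permitted.

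**Working it through.** The protocol gives no sample size, power or effect size for pain or analgesic use, so there is no figure to reproduce. The check sets the texts side by side and does simple timing arithmetic.

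**1. VAS schedules**

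| Time | Section 2.2 | Section 3.10 |
|---|---|---|
| Day 0 | yes, moment not stated | not named |
| Weekly to day 30 | no | yes, start not stated |
| 30 days | yes | only as the end of the weekly period |
| 3, 6, 12 months | yes | yes |

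The sections agree only from 3 months onward.

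**2. Gap between the pain and the first reading**

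Inputs: pain lasting about 2 hours with MAL (Justification); weekly readings for up to 30 days (section 3.10). The start of the weekly series is an assumption, so the range is shown.

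- Start at day 7: readings on days 7, 14, 21 and 28. The first is 7 × 24 = 168 hours after treatment, and 168 / 2 = 84 times the stated duration of pain.
- Start at day 0, marked at or soon after the end of illumination: the reading falls inside the painful period.
- Start at day 0, marked before treatment: the reading misses the pain, and the next comes at 168 hours.

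So the measure works or fails depending on a detail that neither section fixes. Section 2.2 names day 0 but does not place it relative to illumination.

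**3. Analgesic window and content**

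- Objective: 1 week. Paracetamol prescription: 3 days. Evaluation: end of study, with follow-up to 12 months, or about 52 weeks.
- Counted: paracetamol. Permitted but given no counting rule: dipyrone, ibuprofen, ketorolac. A paracetamol-allergic participant given dipyrone or ibuprofen would contribute no paracetamol tablets, whatever the pain. A participant who goes on to ketorolac would have those doses left out.

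**4. Length of the VAS line**

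Taking a marking error of 1 mm as an illustration (the protocol gives none), the error is 1/10 = 10% of the range on a 10 mm line and 1/100 = 1% on a 100 mm line. End labels of 0 and 10 suggest that 10 cm was meant.

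**5. FACE-Q**

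Section 3.7 and the FACE-Q text agree on a baseline. Only the follow-up differs: 6 months against 30 days.

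**The case against.** The strongest reply is that the protocol does plan a treatment-day reading, because section 2.2 lists day 0, and that the weekly series in section 3.10 has no stated start and could begin that day. This stands. The 168 hours follow from one reading of one section, so the defect is an unresolved conflict and an undefined moment on day 0. It is not a proven absence of any early reading.

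A reader might infer that the trial would find no tolerability difference whatever the truth. The documents do not support that. Participants keep a diary of adverse effects, with itching among its examples, and section 2.2 adds researcher notes. These capture some tolerability. They do not yield a pain score, and pain is not among the diary's listed examples.

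A reader might also take the 7.4 versus 0.3 pain scores quoted in the introduction as the contrast at stake. Those scores compare a fabric-based illumination protocol with conventional treatment. Here all four arms share the same lamp and light dose. The figures show that pain can be high at the end of conventional illumination; they say nothing about 8% against 16%, or 1 hour against 3.

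Nor does it follow that participants with the worst pain are broadly undercounted. Dipyrone and ibuprofen are tied to allergy, not severity. Ketorolac follows failure of the earlier medication, so most who take it would already have paracetamol tablets counted; only their ketorolac doses are lost.

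Finally, the blister pack comes to each appointment, so interim counts are possible, and the end-of-study wording may describe when the count is evaluated. That is fair, but no earlier count is specified. The VAS readings at 3, 6 and 12 months do no harm, and dropping them would be only a preference.

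**Conclusion.** The point holds as a conflict between sections with a practical consequence. If section 3.10 is followed and the weekly series starts at day 7, the first VAS comes about 168 hours after an event the protocol says lasts about two hours. A real difference in treatment pain would then probably be missed on this measure. The conclusion rests on the protocol's own account of the pain's duration, on the VAS rating current pain only, and on the assumed day-7 start. It does not extend to all tolerability data.

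The analgesic outcome has two incompatible windows, and its paracetamol-only definition omits three drugs the protocol permits. The documents do not allow the size of that undercount to be estimated. The line length is probably a unit slip, and the FACE-Q timing is a separate inconsistency. All of this concerns secondary outcomes and should be corrected, because it determines which data are collected.

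**What to change.** 1. Give sections 2.2 and 3.10 one VAS schedule. It should include a day-0 mark at a stated moment, at or just after the end of illumination, during the existing treatment visit. Keep the later readings and state the day on which the weekly series starts. Say who hands over the scale on day 0, since section 3.6 keeps the data collector blind and section 3.10 has one operator giving the VAS instructions.
2. Correct the line length, presumably to 10 cm (100 mm).
3. Define the analgesic outcome in both sections as all analgesics taken in the first 7 days: any drug, yes or no, and number of doses. Add an item to the participant diary and count the blister pack at the first follow-up visit. The diary item supplies the 7-day window; the pack count is a cross-check on paracetamol.
4. Align the FACE-Q follow-up time across sections 2.2 and 3.10 and the Abstract, keeping the baseline.

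The cost is rewording plus one or two extra data items. The diary needs a small addition, because it now covers adverse effects and not doses. No change to any analgesic rule is proposed; the point is only that what is measured should cover what the protocol allows.

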## Participants who meet the study's inclusion criteria will be invited to attend the clinical outpatient clinic at UNINOVE, São Paulo, Brazil, to receive dermatological treatment from the dermatologist (principal investigator) between March 2024 and October 2024 (end of treatments). The final one-year follow-up will occur in October 2025. Those who agree to participate will sign the Informed Consent Form (ICF) after a detailed verbal and written explanation provided by the principal investigator.

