**Medication Treatment**

All participants will receive a prescription for pain management if needed:
• Paracetamol every 6 hours for 3 days, only if pain occurs.

Paracetamol is a potent non-opioid analgesic with central action, which will relieve pain when necessary. It is the preferred medication for treating mild to moderate pain, whether acute or chronic. It is effective and has a better safety profile compared to other non-opioid analgesics. In the United States, it is the most prescribed medication for acute pain. Studies show that paracetamol is effective in relieving postoperative pain. In a large study, about half of the patients who received paracetamol achieved at least 50% pain relief within 4 to 6 hours, compared to only 20% of those who received a placebo. This indicates that paracetamol works well for many people. The side effects of paracetamol (such as nausea, vomiting, and drowsiness) are generally mild to moderate and are more related to surgical procedures than to the medication itself (SACHS, 2005; TOMS, 2010).

If the participant is allergic to paracetamol, as indicated by anamnesis, dipyrone 500 mg every 6 hours can be prescribed as an alternative. Dipyrone, widely used in Brazil, has been banned in many European countries and the United States due to severe allergic reactions and the risk of agranulocytosis (a potentially fatal condition). However, studies show that dipyrone has similar efficacy to other non-opioid analgesics in relieving postoperative pain. A 2010 Cochrane review by Ramacciotti et al. revealed that an oral dose of 500 mg provided at least 50% pain relief in 70% of patients within 4 to 6 hours. Furthermore, dipyrone showed comparable efficacy to ibuprofen. In cases of tension headaches and migraines, dipyrone also proved effective. Although rare, its adverse effects are generally mild (EDWARDS, 2010).

In the last case, 400 mg of ibuprofen every 6 hours can be prescribed. In a study evaluating postoperative pain control, single doses of ibuprofen (200 mg and 400 mg) showed at least 50% pain relief compared to placebo. The use of more soluble ibuprofen salts was even more effective. Adverse events were rare and like the placebo (WAHBA, 2004).

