Participants will be instructed to contact the physician and the principal investigator via mobile phone if necessary or if they have questions regarding the study. All participants will leave the clinic with the prescribed medication but will only take it if necessary in cases of severe pain that does not improve with the previously recommended medication:

• Toragesic® (Ketorolac Tromethamine) 10 mg every 6 hours (maximum dose for elderly over 65 – 40 mg/day).

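### Analgesic use is an objective for the first week after treatment, but the outcome is an end-of-study paracetamol count that cannot isolate that week and leaves out the step-up drug

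*Protocol*

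**What the plan says.** **Objective.** Protocol section 2.2 lists: "To evaluate the amount of analgesics consumed weekly during the first week after treatment". It refers to analgesics in general and to the first week.

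**Outcome.** Protocol section 3.10, Rescue Medication, opens: "Rescue medication will be assessed by the standardized amount of analgesics consumed (paracetamol", so paracetamol is the only drug in the parenthesis. On the pack it says: "Participants are instructed to keep the blister pack until the end of the experiment and bring it to each appointment". On timing it says: "At the end of the study, the number of tablets used will be evaluated in each group as a pain measurement parameter". Dipyrone and ibuprofen appear there only as alternatives in reported allergy.

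**Drugs available.** The Medication Treatment section says: "All participants will receive a prescription for pain management if needed". The paracetamol line reads: "Paracetamol every 6 hours for 3 days, only if pain occurs". Dipyrone and then ibuprofen follow as alternatives. The section ends with ketorolac as a step-up drug. Participants leave the clinic with it and "will only take it if necessary in cases of severe pain that does not improve with the previously recommended medication".

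**Length of follow-up.** Section 3 has treatments ending in October 2024 and states: "The final one-year follow-up will occur in October 2025".

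**The concern.** The objective and the outcome that is meant to serve it differ on two things: the period covered and the drugs covered. A single count at 12 months pools the first week with everything taken from the pack afterwards. A count of paracetamol alone omits the drug reserved for pain that the first-line medication did not relieve.

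This matters because the Justification (section 1) rests partly on tolerability. It calls for protocols that mitigate adverse events such as pain, and says lower concentrations could reduce adverse effects. First-week analgesic use is a natural cumulative measure of acute treatment pain. If it is not recorded by drug and date at the time, no later analysis can recover it. For that reason this cannot be left to a statistical analysis plan.

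**Working it through.** The protocol gives no figure for this outcome, so there is none to reproduce. The check compares the passages and adds a little arithmetic.

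**1. Window**
- Objective (section 2.2): first week, 7 days.
- Outcome (section 3.10): end of study, about 365 days after treatment.
- Share of the counted period that belongs to the objective: 7/365 = 1.9%.
- Paracetamol prescription (Medication Treatment): 3 days, so 3/365 = 0.8% of the period and at most (24/6) × 3 = 12 scheduled doses.
- Interim counts: the pack comes to each appointment, but no count at any visit is stated. Section 3.10 has weekly visual analog scale (VAS) assessments through the first 30 days. Section 2.2 lists the VAS at day 0 and day 30 with nothing between. A count near day 7 may therefore be possible, but none is specified.

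**2. Drugs**

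| Drug | Permitted in Medication Treatment | In the section 3.10 count |
|---|---|---|
| Paracetamol | yes | yes |
| Dipyrone | yes, as alternative | named for allergy, no counting rule |
| Ibuprofen | yes, as alternative | named for allergy, no counting rule |
| Ketorolac | yes, step-up for severe unrelieved pain | not mentioned |

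Three of the four permitted drugs are outside the stated count.

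**3. Direction of the error from the drugs left out**

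Let T be all analgesic doses, P the paracetamol tablets counted and O the doses of other drugs, so P = T − O. The difference between arms in the recorded count is ΔP = ΔT − ΔO. If the more painful arm also uses more step-up drug, ΔO has the same sign as ΔT and ΔP is smaller than ΔT, so the difference is compressed. For ΔP to vanish or reverse, ΔO would have to equal or exceed ΔT. That would require the more painful arm to take no more paracetamol than the other arm.

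**4. Illustration of noise from later use (assumed inputs, not in the protocol)**

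Assume 36 per group (section 3.1), a true first-week difference of 2 tablets, a first-week SD of 3, and independent unrelated tablets later in the year with SD s. For two groups at two-sided 5%:

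Power = Φ( 2 / [√(9 + s²) × √(2/36)] − 1.96 )

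| s | √(9 + s²) | Power |
|---|---|---|
| 0 (first week only) | 3.00 | 81% |
| 1 | 3.16 | 77% |
| 2 | 3.61 | 65% |
| 4 | 5.00 | 40% |
| 6 | 6.71 | 24% |

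The loss runs from slight to severe depending on s, about which the protocol says nothing.

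**The case against.** The strongest reply is that this is a supporting outcome, absent from the abstract's list of secondary outcomes; that pain is measured directly by VAS; that the pack is brought to appointments, so an early count is open to the investigator; and that coding rules for a few allergic participants can go in an analysis plan. Much of this is fair. It lowers the stakes but does not repair the mismatch: the section 3.10 text still fixes the evaluation at the end of the study and limits it to paracetamol.

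Several stronger readings are tempting, and the documents do not support them:

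- **No contact before day 30.** A reader might infer this from the main visit schedule. The weekly VAS assessments in section 3.10 leave it open.
- **A second paracetamol supply outside the blister.** The prescription and the blister may be the same supply. Nothing states that there are two.
- **Dipyrone or ibuprofen users scored as zero.** The text gives no rule for them, which is not the same as scoring them zero.
- **A more painful arm showing an equal or lower count.** Step-up users will normally have taken the first-line drug already, so they still contribute tablets. Compression is likely if step-up use differs between arms. Reversal is possible but not shown.
- **Treatment pain going unmeasured.** The VAS measures it. What fails is the measure of first-week analgesic use.
- **The power figures as evidence.** They rest on invented means and SDs and a two-group comparison, whereas Results Analysis plans two-way ANOVA or Kruskal-Wallis. They also assume that later unrelated use comes out of the study pack. Participants with other tablets at home need not use it.

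**Conclusion.** The point stands in a limited form. Section 2.2 asks for first-week use of analgesics. Section 3.10 delivers a paracetamol count at the end of a 12-month study, with no count specified at or near day 7, no rule for two permitted alternatives and no mention of the step-up drug. Followed as written, it cannot isolate the first week, and it misses part of the use among participants with the most severe pain. It is therefore not a valid measure of first-week analgesic use.

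What follows directly from the text is that the objective covers 1.9% of the counted period and that three of the four permitted drugs lie outside the stated count. Compression of differences between arms rests on the assumption that step-up use rises with pain, which agrees with the stated condition for taking that drug. The size of any power loss is unknown: the 81% to 24% range is illustrative only. The primary outcome is not affected. The mismatch should be corrected because the missing data cannot be reconstructed afterwards.

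**What to change.** Reconcile section 2.2, section 3.10 (Rescue Medication) and Medication Treatment on the window and on which drugs are counted. Specifically:

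1. Define the outcome as the number of analgesic doses of any drug taken on days 0-7, recorded by drug and date on a page added to the diary participants already keep for adverse effects.
2. Report alongside it the proportion of participants who used the step-up drug.
3. Collect the page and check the blister by the 30-day visit, or earlier if the weekly VAS assessments prove to be appointments.
4. Drop the end-of-study tablet count as the pain measure.

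The cost is one diary page and a wording change, with no added visit. The small downside is reliance on self-report, which the blister check partly offsets for paracetamol. The change affects only what is recorded and leaves the drugs and doses offered as they are.

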## **3.1. 3.1. Sample Size Calculation**

Considering the study by Braathen et al. (2008), which reported a variation in complete lesion response rates ranging from 64% to 91% after 3 months in the 8% (1 and 3 hours) and 16% (1 and 3 hours) groups, with a 95% confidence level and 80% power to detect differences between groups, the minimum sample size will be 36 participants per group, for a total of 144 participants. This result was obtained using a chi-square test for differences in proportions.

Figure 1 - Study Flowchart

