**RESULTS ANALYSIS**

Initial descriptive analyses will be performed considering all variables measured in the study, both quantitative (mean and standard deviation) and qualitative (frequencies and percentages). If the data follow a normal distribution, they will be subjected to two-way ANOVA, and the data will be presented as means ± standard deviation (SD). Otherwise, they will be presented as medians and interquartile ranges and compared using the Kruskal-Wallis test. Categorical variables will be evaluated using the chi-square test, Fisher's exact test, or the likelihood ratio test. For all tests, a 5% significance level or the corresponding p-value will be adopted. All analyses will be conducted using the SAS for Windows statistical program, version 9.1.

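### The ordered four-grade skin scale is, on the natural reading, left to tests that ignore order, and its lowest grade cannot separate no change from small improvement

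*Protocol*

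**What the plan says.** Section 3.10 of the protocol lists the skin texture, wrinkle and pigmentation evaluation among the secondary outcomes. The scale "classifies improvements as minimal (<25%), moderate (25%-50%), significant (51%-75%), and excellent (>75" per cent. On timing: "This evaluation will be conducted at 30 days, 3, 6, and 12 months".

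RESULTS ANALYSIS describes all variables as "both quantitative (mean and standard deviation) and qualitative (frequencies and percentages"), with no class for ordinal data. Quantitative data go to two-way ANOVA if normal. "Otherwise, they will be presented as medians and interquartile ranges and compared using the Kruskal-Wallis test". The next sentence deals with categorical data: "Categorical variables will be evaluated using the chi-square test, Fisher's exact test, or the likelihood ratio test". The abstract says the same. On the error level: "For all tests, a 5% significance level or the corresponding p-value will be adopted".

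Neither section says which of these branches governs the skin scale.

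**The concern.** A grade recorded as one of four bands is most naturally a qualitative variable, summarised by frequencies and percentages and sent to the tests for categorical data. The Pearson chi-square, Fisher's exact and likelihood ratio tests all give the same p-value if the grade labels are shuffled. With four arms and four grades they look for any pattern at all on 9 degrees of freedom, when the question is whether one regimen gives better skin than another. That costs power whenever the treatment moves the whole distribution up or down.

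The second matter is recording. The bottom band is anything under 25%, with no lower limit. A participant with 0% change can only be placed in *minimal*, and one whose skin is worse has no stated place. If this is not recorded at the visit, no later analysis can recover it.

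**Working it through.** **1. The plan's own figure.** Section 3.1 cites a "variation in complete lesion response rates ranging from 64% to 91% after 3 months" and sizes the trial "with a 95% confidence level and 80% power to detect differences between groups", giving 36 per group. With p1 = 0.64, p2 = 0.91, mean 0.775, two-sided 5% (assumed; sidedness is not stated) and pooled variance:

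n = [1.960 × √(2 × 0.775 × 0.225) + 0.842 × √(0.64 × 0.36 + 0.91 × 0.09)]² / 0.27² = (1.157 + 0.470)² / 0.0729 = 36.3, so 37.

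Power at 36 is 79.6%. The figure reproduces to within one participant. It concerns complete response and says nothing about power for the skin scale, so an effect has to be assumed below.

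**2. Why ordering matters: one worked case.** Assume grades of 20/30/30/20% in both 8% arms and a proportional-odds shift with odds ratio 2.0 in both 16% arms. The odds of being at or below each cut are 0.25, 1 and 4. Halved, they are 0.125, 0.5 and 2, so the 16% arms have 11.1/22.2/33.3/33.3%. The averages over arms are 15.6/26.1/31.7/26.7%.

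- Pearson chi-square: noncentrality = 36 × Σ over arms and grades of (p − p̄)²/p̄ = 5.19. Degrees of freedom (4−1)(4−1) = 9, critical value 16.92, power 29%.
- Kruskal-Wallis: with mid-rank scores from the average distribution, the arm means are 0.447 (twice) and 0.553 (twice), and the score variance is 0.0773. Noncentrality = 36 × 4 × 0.0528² / 0.0773 = 5.19. Degrees of freedom 3, critical value 7.81, power 46%.

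The signal is the same in both tests. The chi-square spreads it over 9 degrees of freedom instead of 3.

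If instead one arm alone shifts, with odds ratio 3, the noncentralities are 9.56 and 9.24 and the powers 54% and 72%. Simulating both settings (5,000 trials each) gave 28% against 46%, and 53% against 74%.

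**3. Wider range.** Simulation with 4,000 trials per setting, 36 per arm, three assumed baselines (25/25/25/25, 40/30/20/10, 10/20/30/40). Each cell gives the range over baselines, in per cent; the last column is in percentage points. In the graded patterns the two middle arms are shifted by half the log odds ratio.

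| Assumed shift | Pearson | Likelihood ratio | Kruskal-Wallis | Loss, Pearson |
|---|---|---|---|---|
| Four arms, graded to odds ratio 3 | 31–36 | 38–39 | 49–56 | 18–20 |
| Four arms, graded to odds ratio 4 | 49–58 | 55–61 | 69–77 | 19–21 |
| Four arms, one shifted, odds ratio 3 | 47–55 | 53–58 | 67–75 | 19–21 |
| Two arms only, odds ratio 2 | 22–23 | 26 | 34–36 | 12–13 |
| Two arms only, odds ratio 3 | 48–55 | 53–57 | 67–72 | 17–19 |
| Two arms only, odds ratio 3.5 | 59–67 | 64–69 | 77–83 | 16–18 |

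With no effect, rejection was 4.7–5.3% for Pearson, 4.8–5.4% for Kruskal-Wallis and 6.3–6.9% for the likelihood ratio test. The likelihood ratio test therefore loses somewhat less power (about 8 to 17 points), but partly because it rejects too often. Fisher's exact test and the proportional-odds model were not simulated.

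**4. The floor of the scale.** The four bands are under 25%, 25–50%, 51–75% and over 75%. A change of 0% satisfies only the first. A negative change either satisfies the first or is outside a scale of improvement; the text does not say which.

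**The case against.** The strongest reply is that the protocol assigns this scale to no test by name, and that Kruskal-Wallis, one of the two remedies proposed here, already appears in the same paragraph. A statistical analysis plan could settle the matter. This stands in part: the assignment to the unordered tests is an inference. But the protocol itself fixes the tests for categorical data, and Kruskal-Wallis is reserved for data that were candidates for ANOVA. A reader following the text would reach for chi-square.

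It is also fair that this is a matter of efficiency on a secondary outcome. The Pearson chi-square is valid, and it can detect differences that do not run in one direction, which an ordered test may miss.

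Four stronger readings are tempting and should not be drawn:

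- *Worsening is recorded as improvement.* The text gives worsening no grade; it does not place it in *minimal*.
- *The proportion improved will be overstated.* No such endpoint is defined.
- *Professional and participant ratings are pooled.* The protocol says that both groups rate; it does not say that their scores are combined.
- *A larger gain is available from an ordered comparison of 16% with 8%, ignoring incubation time.* Such a comparison mixes the benefit of ordering with that of pooling arms. If only one arm shifts (odds ratio 3, baseline 20/30/30/20%), its power is 43%, below the chi-square in the same setting (53%).

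**Conclusion.** The point holds as a minor one. On the natural reading, an ordered outcome is to be tested by methods that discard its order, and a better method is available at almost no cost. The loss with the Pearson chi-square is about 12 to 21 percentage points against Kruskal-Wallis at 36 per arm. That range rests on assumed grade distributions and on shifts in one consistent direction; the documents supply neither, so it illustrates the loss and does not predict it. The chi-square's type I error and the primary outcome are unaffected.

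The missing floor needs no assumption: as defined, the scale cannot separate no change from small improvement, and it gives worsening no stated grade.

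**What to change.** In RESULTS ANALYSIS, add one sentence: the skin texture, wrinkle and pigmentation grades are analysed by a method that uses their order. This can be Kruskal-Wallis across the four arms, or a proportional-odds model with concentration, incubation time and their interaction, reported as odds ratios with 95% confidence intervals.

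In section 3.10 and on the rating form, add separate boxes for no change and for worse. Merging them with the lowest band still allows the published four grades to be tabulated.

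The cost is one sentence and two tick-boxes, with no added visits or participants. There is a small downside: the proportional-odds model brings an assumption to check, and any ordered test is less sensitive to non-monotone differences.
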